## 6.2 Exclusion criteria

Patients presenting with any of the following will not be included in study:

- 1) Uncontrolled diabetes
- 2) H/o myocardial infarction within the previous 3 months
- 3) H/o cerebrovascular event within previous 3 months
- 4) Uncontrolled arrhythmias
- 5) H/o Heart failure
- 6) Patients with severe impaired renal function serum creatinine levels > 5.3 mg/dl and / or serious liver disorders
- 7) Patients unwilling to give informed consent.
- 8) Patients with history of hypersensitivity to Indapamide or Amlodipine
- 9) Any contraindication to Thiazide type diuretic and/or CCB
- 10) Pregnancy or lactation
- 11) Patients with any other condition or disease, which in opinion of the investigator could preclude evaluation of response to study medication or hamper the safety of the trial participant.
- 12) Patients previously enrolled in similar trial in the last 6 months.

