#### 4.4.3 Follow up visit (Visit 2, Day 15 $\pm$ 5 days)

At the follow-up visit 2, the investigator shall conduct the clinical and vital examination of the patient. He shall check the compliance to the study medication and shall interview the patient for any undesirable effects experienced since the last visit. At each visit, the doctor will also confirm that each patient is complying with the prescription and not missing any doses. The unused study medicine shall be collected from the patient. The investigator shall dispense the medications for the next 15  $\pm$  5 days to the patients.

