#### 4.4.4. Follow-up visit (Visit 3, Day 30 $\pm$ 5 days)

At the follow-up visit 3, the investigator shall conduct the clinical and vital examination of the patient. He shall check the compliance to the study medication and shall interview the patient for any undesirable effects experienced since the last visit. At each visit, the doctor will also confirm that each patient is complying with the prescription and not missing any doses. The unused study medicine shall be collected from the patient. The investigator shall dispense the medications for the next 15  $\pm$  5 days to the patients. Clinical and vital examination, Compliance to study drug, AEs if any shall be recorded.

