#### 4.4.6 Laboratory Assessments

The laboratory investigations as under will be performed during screening and at end of study (Visit 4, Day 45± 5 days). All tests will be performed at laboratories associated with trial centers or otherwise defined before the initiation of the trial. 5 mL of blood and 30 mL of urine will be collected, each at visit 1 and visit 4 (total blood loss for each patient = not more than 10 mL)

The laboratory test will include -

|                |   |                                                                                                                 |
|----------------|---|-----------------------------------------------------------------------------------------------------------------|
| Hematology     | - | CBC, ESR                                                                                                        |
| Biochemistry   | - | Total Bilirubin, AST, ALT, Serum Creatinine, Blood urea, Fasting blood sugar, Serum Electrolytes, Lipid profile |
| Urine Analysis | - | Routine & microscopy                                                                                            |
| ECG            | - | Chest                                                                                                           |

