## 23. Patient Activity Chart

| Activity                                               | Pre Selection Visit | Baseline visit, Visit 1 (D 0 ) | Follow-up visit, Visit 2 (D 15 ) | Follow-up visit, Visit 3 (D 30 ) | End of study visit, Visit 4 (D 45 ) |
|--------------------------------------------------------|---------------------|-------------------------------------------|---------------------------------------------|---------------------------------------------|------------------------------------------------|
| Informed Consent                                       | X                   | --                                        | --                                          | --                                          | --                                             |
| Blood pressure, Heart rate                             | X                   | X                                         | X                                           | X                                           | X                                              |
| Laboratory investigations                              | X                   | --                                        | --                                          | --                                          | X                                              |
| Eligibility Criteria                                   | X                   | X (based on lab reports)                  | --                                          | --                                          | --                                             |
| Demography, clinical characteristics & Medical history | X                   | --                                        | --                                          | --                                          | --                                             |
| Clinical examination                                   | --                  | X                                         | X                                           | X                                           | X                                              |
| Study medication to be provided                        | --                  | X                                         | X                                           | X                                           | --                                             |

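### The only numeric renal limit, serum creatinine above 5.3 mg/dl, corresponds to very low estimated renal function and, if 'severe' means below 30 mL/min, lets severely impaired patients pass that check

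*Protocol*

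**What the plan says.** Protocol section 6.2, exclusion 6, removes "Patients with severe impaired renal function serum creatinine levels > 5.3 mg/dl and / or serious liver disorders". No estimated GFR or creatinine clearance appears anywhere in the protocol, and no other renal criterion carries a number.

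Two further exclusions in section 6.2 can bear on renal patients. Exclusion 9 is mandatory: "Any contraindication to Thiazide type diuretic and/or CCB". Exclusion 11 covers any other condition "which in opinion of the investigator could preclude evaluation of response to study medication or hamper the safety of the trial participant". Neither gives a renal value. The product fact sheet mentioned in sections 10 and 11 is not reproduced in the protocol.

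On timing, section 4.4.6 states: "The laboratory investigations as under will be performed during screening and at end of study". The panel includes serum creatinine, blood urea and serum electrolytes. The activity chart in section 23 has eligibility confirmed at Visit 1 from the laboratory reports. It schedules no laboratory tests at Visits 2 and 3. Those visits are clinical. For Visit 2, section 4.4.3 says: "At the follow-up visit 2, the investigator shall conduct the clinical and vital examination of the patient". For Visit 3, section 4.4.4 says: "Clinical and vital examination, Compliance to study drug, AEs if any shall be recorded".

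**The concern.** A single raw creatinine value means different things in different people. The same 5.3 mg/dl reflects much lower function in a small elderly woman than in a heavy young man. The protocol attaches the word 'severe' to this figure, which invites a site to treat anything below it as acceptable. If the figure sits well into the range usually meant by severe impairment, the one renal criterion that can be checked against a laboratory report does not do its job.

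What is at stake is patient safety. Every enrolled patient receives indapamide SR 1.5 mg plus amlodipine 5 mg daily until Day 45 ± 5. With no creatinine or electrolytes scheduled between the pre-treatment sample and Visit 4, the entry check is the only scheduled laboratory look at renal function before the end of treatment. Safety and tolerability is also the trial's secondary objective (section 3.2). No sample size, power or alpha figure depends on this point.

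**Working it through.** **Inputs.** From the protocol: the limit of 5.3 mg/dl (5.3 × 88.4 = 468.5 µmol/L). The protocol gives no derivation for it, so there is no planned figure to reproduce. Section 6.1 sets no age or weight limits, so the following are assumptions: ages 30, 40, 50, 60 and 70; weights 50, 60, 70, 80 and 90 kg; both sexes. That makes 50 profiles for Cockcroft-Gault and 10 age-sex profiles for the formulas that do not use weight. These are assumed profiles, not patients.

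**Formulas** (SCr in mg/dl).
- Cockcroft-Gault: (140 − age) × kg / (72 × SCr), × 0.85 for women.
- MDRD, 4-variable, race term set to 1: 175 × SCr^(−1.154) × age^(−0.203), × 0.742 for women.
- CKD-EPI 2021, as a cross-check: 142 × (SCr/k)^(−1.200) × 0.9938^age, with k = 0.9 for men and 0.7 for women, × 1.012 for women. This form applies because SCr exceeds k throughout.

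**Step 1: function at the protocol's limit, SCr = 5.3.**
- Cockcroft-Gault, lowest (woman, 70 y, 50 kg): 70 × 50 × 0.85 / (72 × 5.3) = 2975 / 381.6 = 7.8 mL/min.
- Cockcroft-Gault, highest (man, 30 y, 90 kg): 110 × 90 / 381.6 = 25.9 mL/min.
- MDRD: 8.0 (woman, 70 y) to 12.8 (man, 30 y) mL/min/1.73 m².
- CKD-EPI: 8.2 to 14.0 mL/min/1.73 m².

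All 50 Cockcroft-Gault profiles and all 10 profiles under each of the other two formulas are below 30.

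**Step 2: function at values that exclusion 6's number allows.**

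| SCr (mg/dl) | Cockcroft-Gault, mL/min | Below 30 | MDRD, mL/min/1.73 m² | Below 30 |
|---|---|---|---|---|
| 3.0 | 13.8-45.8 | 34 of 50 | 15.4-24.7 | 10 of 10 |
| 4.0 | 10.3-34.4 | 47 of 50 | 11.1-17.7 | 10 of 10 |

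**Step 3: creatinine that corresponds to a given definition of 'severe'.** For Cockcroft-Gault, SCr = (140 − age) × kg × sex factor / (72 × target). With a target of 30, the extremes are 2975 / 2160 = 1.4 and 9900 / 2160 = 4.6 mg/dl.

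| Definition | Cockcroft-Gault (median of grid) | MDRD | CKD-EPI | Protocol |
|---|---|---|---|---|
| below 30 | 1.4-4.6 (2.6) | 1.7-2.5 | 1.8-2.8 | 5.3 |
| below 15 | 2.8-9.2 (5.19) | 3.1-4.6 | 3.2-5.0 | 5.3 |

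At 30, every matching creatinine is below 5.3. At 15, MDRD and CKD-EPI still lie wholly below 5.3, but 23 of the 50 Cockcroft-Gault profiles lie above it.

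**Step 4: wider ranges.** For ages 18-85 and weights 50-100 kg at 5.3 mg/dl, Cockcroft-Gault gives 6.1 (woman, 85 y, 50 kg) to 32.0 mL/min (man, 18 y, 100 kg), and MDRD gives 7.7 to 14.2. A profile exceeds 30 mL/min at the limit only at the young, heavy extreme.

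**The case against.** The strongest reply is that the result rests on a definition brought in from outside. The protocol never says that 'severe' means below 30 mL/min, and nothing else in it contradicts 5.3 mg/dl. With below 15 as the definition and Cockcroft-Gault as the formula, the grid median of 5.19 mg/dl almost equals the protocol's figure, so 5.3 would be a fair single-value proxy. This stands as a limit on the point. It does not remove it: on that same reading, 27 of 50 Cockcroft-Gault profiles and all 10 MDRD profiles are already below 15 at 5.3 mg/dl.

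Second, passing exclusion 6 is not the same as being eligible. The investigator has the laboratory results before dosing, exclusion 9 is mandatory, and exclusion 11 covers safety. If the product fact sheet lists severe renal impairment as a contraindication, exclusion 9 bars these patients whatever exclusion 6 says. This also stands, and it cannot be settled without that sheet. Neither exclusion, however, gives the site a value to apply.

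Third, the wording is open. No connector joins the phrase on renal function to the creatinine figure. The figure may define 'severe', or severe impairment may be a clinical criterion in its own right with the creatinine value as an added trigger. On the second reading, a clinically severe patient below 5.3 mg/dl is already excluded. Both readings are possible, and the ambiguity is itself a reason to rewrite the line.

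A reader might go further and infer that severely impaired patients will be enrolled, that exclusion 6 is the only renal safeguard, or that 5.3 is a typing or unit error. The documents support none of these: the other exclusions may act, and no source for the figure is given.

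**Conclusion.** The point holds in conditional form. The calculation shows that 5.3 mg/dl, the only renal limit with a number, corresponds to about 8-26 mL/min by Cockcroft-Gault and 8-13 mL/min/1.73 m² by MDRD over the main assumed ranges (6-32 and 8-14 over the wider ones). If 'severe' means below 30 mL/min, there is a band of creatinine values, starting somewhere between roughly 1.4 and 4.6 mg/dl and ending at 5.3, in which a severely impaired patient passes the numeric check. If it means below 15, the conclusion depends on the formula.

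Whether such a patient would actually be treated depends on exclusion 9, exclusion 11 and how the site reads the wording of exclusion 6. A demonstrated safety failure is therefore not established, and the number affected among the 240 planned patients cannot be estimated. The correction is worth making because it closes a possible safety gap at little cost. Confidence is medium.

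**What to change.** In exclusion 6, replace the creatinine figure with one limit from one named formula. For example: severe renal impairment, defined as estimated GFR below 30 mL/min/1.73 m² by 4-variable MDRD from the screening creatinine, age and sex, and/or serious liver disorders. The sponsor's clinical team should confirm the value against the product fact sheet before the amendment is issued. Stating that the limit defines the term also removes the ambiguity in the wording. Keep exclusions 9 and 11 as they are.

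The cost is a one-line eligibility amendment. Creatinine is already in the screening panel (section 4.4.6) and demography is taken at the pre-selection visit (section 23). MDRD needs no body weight, so no new test or visit is required. The downside is some additional screen failures, in a number that the documents do not allow one to estimate.

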## 7. Study conduct

The study will be conducted as per the GCP guidelines and the “Ethical Guidelines for Biomedical Research on Human Participants” issued by ICMR and the other regulations in force in India.

## 8. Study treatment

Each eligible patient shall receive the study medication under evaluation from the participating investigator. The dose of this FDC is once daily in the morning.

## 9. Forbidden medication

Any other concurrent antihypertensive medication is forbidden during the study period.

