#### 4.4.5 End of Study (Visit 4, Day 45 $\pm$ 5 days)

This is the end of study visit. The investigator shall conduct the clinical and vital examination of the patient. He shall check the compliance to the study medication and shall interview the patient for any undesirable effects experienced since the last visit. At each visit, the doctor will also confirm that each patient is complying with the prescription and not missing any doses. The unused study medicine shall be collected from the patient. Additionally laboratory investigations (section 4.4.6) and ECG shall be repeated at the end of study. The investigator shall prescribe the most appropriate medicine for the treatment of hypertension to the patient.

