### 5. Study population

240 patients (30 patients per centre) will be included in the study satisfying the eligibility criteria as per the protocol, with an objective to obtain at least 200 patients completing the study.

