### 6. Eligibility Criteria

#### 6.1 Inclusion Criteria

1. Newly diagnosed untreated hypertensive patients having a baseline blood pressure  $\geq 160/100$  mmHg) OR
2. Uncontrolled patients of hypertension with a baseline blood pressure  $\geq 140/90$  mmHg on monotherapy with a Calcium Channel Blocker (CCB)
3. Patients of either sex

4. With confirmed diagnosis of Stage II/ III (moderate to severe) hypertension, as per JNC 7 guidelines

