## 10. Other concomitant medication

All other concomitant medicines as per the discretion of the investigator will continue except those that are contraindicated as per product fact sheet.

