## 11. Adverse Events

All adverse events whether *expected* (as stated in the proposed product fact sheet) or *unexpected* (those not mentioned in the product fact sheet) reported by patients or observed must be recorded in the CRFs with information about severity i.e. whether

- Mild: no significant interference with usual activities;
- Moderate: significant interference with usual activities or;
- Severe: prevents usual activities, date of onset duration and action taken regarding study drug.

Relation of adverse events to study medication will be described as unrelated, probable or possible.

- Unrelated: a reaction that does not follow a reasonable temporal sequence from the administration of the medicine; is not known adverse reaction pattern of the suspected medicine; could have been produced by the patients clinical state, inter current illness, trauma, accidents etc.
- Probable: A reaction that follows the reasonable temporal sequence from administration of medicine; that follow as a known or expected response pattern to the suspected medicine; and that could not be reasonably explained by the known characteristics of the patient's clinical state
- Possible: reaction that follows the reasonable temporal sequence from administration of medicine; that follows as a know or expected response pattern to the suspected medicine; but that could readily have been produced by a number of other factors including the patients clinical state or other modes of therapy administered to the patients.

Any serious adverse effects must be notified immediately by telephone to the study monitor and subsequently in writing as specified later in this section.

A serious event or reaction (SAE) is any unto odd medical occurrence that at any dose:

- Results in death
- Is life threatening
- Requires inpatient hospitalization or prolongation of existing hospitalization
- Results in persistent or significant disability/incapacity, or
- Is a congenital anomaly/birth defect

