## 19. Early Study Termination

The study will be terminated in case of any safety issues and /or protocol violations. The study may also be discontinued at a center for reason of particularly low recruitment rate, or inadequate data recording or any other issues that may necessarily require study termination. In any case, the investigator shall keep the Ethics Committee updated on the study progress. The sponsor shall keep the regulatory authorities informed about such decisions.

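### Visits 2 and 3 re-dispense the same fixed tablet with no blood pressure condition, and the readable text sets no level at which an individual patient stops before Visit 4

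*Protocol*

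**What the plan says.** Section 9 of the Protocol reads "Any other concurrent antihypertensive medication is forbidden during the study period". Section 10 lets the investigator continue other medicines ("All other concomitant medicines as per the discretion of the investigator will continue"), which does not reopen the choice of antihypertensive. Sections 3.1 and 8 fix one strength, indapamide SR 1.5 mg with amlodipine 5 mg, once daily, with no titration step.

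Blood pressure is measured at every follow-up visit (4.4.2). At Visit 2 (4.4.3), and in the same words at Visit 3 (4.4.4), the instruction is "The investigator shall dispense the medications for the next 15" ± 5 days. No action at either visit depends on the reading. Only at Visit 4 (4.4.5) does the Protocol provide for other treatment: "The investigator shall prescribe the most appropriate medicine for the treatment of hypertension to the patient".

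Inclusion criterion 1 begins "Newly diagnosed untreated hypertensive patients having a baseline blood pressure" and sets a floor of 160/100 mmHg. Criterion 2 sets a floor of 140/90 mmHg on calcium channel blocker monotherapy. Neither states an upper limit. Section 19 deals with ending the study or closing a centre ("The study may also be discontinued at a center for reason of particularly low recruitment rate"), not with an individual patient. Section 5 plans 240 patients "with an objective to obtain at least 200 patients completing the study".

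**The concern.** Very high readings during treatment are foreseeable in this population, and the Protocol schedules two visits at which they would be seen. An investigator who follows the written steps literally would then supply the same tablet again and add nothing until Visit 4. When to stop is left to each investigator at 8 centres (240/30).

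The first stake is patient safety, because severe hypertension may cause no discomfort that would lead a patient to call or withdraw. The second is consistency: without a written level, who stops early depends on the centre. An individual stopping rule is a matter of trial conduct and belongs in the protocol, so an unseen SAP would not be expected to supply it. How stopped patients count in the analysis can be left to the SAP and is not raised here.

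**Working it through.** The Protocol gives no figure on this point to reproduce. The check has three parts.

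**1. Search for an individual stopping level.** The places where one could stand:

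| Place in the Protocol | What it provides | Individual pressure level? |
|---|---|---|
| 4.4.2 | Pressure measured at each follow-up visit; patient told to contact the investigator if troubled | No |
| 4.4.3, 4.4.4 | Examination, compliance and adverse event check, then re-dispensing | No |
| 4.4.5 | Choice of other treatment, at Visit 4 only | No |
| 6.2, exclusion 11 | Investigator may refuse a patient on safety grounds, at entry only | No |
| 7 | GCP and national ethical guidelines apply | No |
| 9 | Ban on concurrent antihypertensives | No |
| 11 | Records "date of onset duration and action taken regarding study drug" for adverse events | No |
| 12 | Patient may opt out at any time | No |
| 19 | Study or centre stops | No |
| 23 | Activity chart | No |
| 4.2, 22 | Flow charts, not available to this review | Unknown |

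**2. Time from a reading to Visit 4.** The windows are Visit 2 at Day 15 ± 5 (10 to 20), Visit 3 at Day 30 ± 5 (25 to 35) and Visit 4 at Day 45 ± 5 (40 to 50).

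- Visit 2 to Visit 4: shortest 40 − 20 = 20 days, longest 50 − 10 = 40 days.
- Visit 3 to Visit 4: shortest 40 − 35 = 5 days, longest 50 − 25 = 25 days.

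**3. Room for early stops.** Section 5 allows 240 − 200 = 40 non-completers, or 40/240 = 16.7%, for all causes together.

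The number of patients who would reach a given ceiling cannot be derived, because the Protocol gives no entry distribution, expected fall or SD of change. Assumed inputs show how little can be said. Take SBP ≥180 or DBP ≥110 mmHg at Visit 2 or 3 as the ceiling.

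- Favourable: mean falls of 25/12 mmHg in untreated patients and 12/6 in those from a calcium channel blocker, SD of change 8/5, 25% untreated. This gives about 0.3 of 240.
- Unfavourable: mean entry pressures of 170/105 and 155/97, falls of 15/7.5 in untreated patients, 8/4 in those from the same calcium channel blocker dose and 4/2 in those stepped down from a higher dose (half of the latter group), SD of change 15/9, 75% untreated. This gives about 60 of 240.

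A range from 0.3 to 60 supports no estimate, and no central value within it means anything.

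**The case against.** The strongest reply is that nothing in the text forbids an investigator from stopping the tablet. A physician measures pressure about every 15 days, open-label, in patients on two active drugs with no placebo or washout. GCP (section 7), the examination at each visit, the advice to make contact, action on study drug after an adverse event (section 11) and the right to opt out (section 12) all leave room to act. Exclusion 11 lets a dangerous entry pressure be refused. Section 5 already expects some patients not to complete. With no comparator arm, uneven stopping across centres matters less than in a randomised trial. All of this stands and limits the weight of the point. None of it sets a level, and exclusion 11 does not reach Visits 2 and 3.

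A reader might infer more than the Protocol supports:

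- **That section 9 bars rescue altogether.** It bars *concurrent* drugs, most naturally read as add-on therapy alongside the study tablet. It does not bar treating a patient who has stopped. A ban on add-on drugs is also a sensible choice here, since an added drug would confound the pressure reduction in 16.1.
- **That no rule exists anywhere.** The flow charts in 4.2 and 22 could carry one. The claim is confined to the readable text.
- **That a known number of patients is at risk.** Every input to such a count is assumed.
- **That patients stepped down from a higher calcium channel blocker dose are a sizeable group.** The Protocol does not give prior doses, so their frequency is unknown.

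**Conclusion.** The point holds in a limited form and is one to consider. The readable Protocol directs re-dispensing at Visits 2 and 3 without a pressure condition, bars add-on treatment, and sets no individual withdrawal level before Visit 4, in a population with no stated upper limit on entry pressure. The size that can be stated is the interval: 20 to 40 days from Visit 2 and 5 to 25 days from Visit 3. The rule would apply to all 240 patients; how many would meet it is unknown. The conclusion rests on the readable text alone and would fall away if either flow chart sets such a level.

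**What to change.** In 4.4.3 and 4.4.4, make re-dispensing conditional on a pressure below a prespecified safety ceiling. Use the mean of the repeat readings already required at each visit (at least two, 4.4.2). An example is to stop at SBP ≥180 or DBP ≥110 mmHg. That value is an illustration and not in the Protocol; the sponsor should confirm it on clinical grounds. A patient at or above the ceiling stops the tablet, has the Visit 4 laboratory tests and ECG at that time, and is treated as in 4.4.5. This preserves end-of-treatment safety data that are otherwise collected only at Visit 4.

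In section 9, clarify that the ban covers add-on therapy while on the study tablet and not treatment after it is stopped. If a flow chart already carries such a rule, repeat it in the text.

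The rule needs no extra visit and no extra reading. A mandatory second-day confirmation, or a limit on the prior calcium channel blocker dose, would add cost and is not needed. The cost is early stops, which share the allowance of 40 non-completers with ordinary dropout. Their number cannot be forecast from the Protocol. Under the unfavourable assumptions above it would exceed 40, so the sponsor should weigh the ceiling against its own data on expected response.
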